### Ethical considerations

Reasonable precautions against harms and steps to mitigate risks will be taken. To minimise the potential risk for adverse effects, participants will be screened for potential contraindications for both tDCS and rTMS treatment prior to providing informed consent. Safety and adverse effects will be closely monitored by study staff over the course of the trial and through ongoing care by the participants’ treating psychiatrist, who will continue to oversee clinical progress and the welfare of his/her patient over the course of the study. Every 6 months reports of any serious adverse events will be monitored by an independent medical monitor.

To ensure confidentiality, all data collected will be de-identified. Where participant consent is provided for data to be re-used and shared with other researchers for future research projects, data will only be provided in a de-identified format and with separate ethics approval. No identifiable information will be reported in any format, thus protecting the confidentiality of participants and other information collected during the study.

### Analysis

#### Populations

The analysis will be completed for the Modified Intention to Treat (mITT) and the Per Protocol (PP) populations. The mITT population will include all participants randomised and who had at least 1 randomised treatment and 1 post baseline rating. The PP population is a subset of the mITT population and will include all participants randomised who fulfil the following criteria: (1) received at least 80% of randomised acute active or sham tDCS or active or sham rTMS treatments over the 8 week treatment period and (2) have an absence of significant protocol deviations (received correct treatment assignment in randomised phase and rTMS dose is correct in at least 80% of randomised treatments).

#### Primary outcomes

The efficacy analysis will be completed for both the mITT and PP population. Descriptive statistics and graphical methods will be used to show variability in the data. The size of the treatment effect for EDE-Q Global scores will be the change in scores from pre-treatment to post 8 weeks treatment for both active treatment arms. The acceptability analysis will be completed in the mITT population. Descriptive statistics will report the number of completed active tDCS and active rTMS treatments in the 8 week randomised controlled period.

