### Current study

Despite initial promising findings, the potential therapeutic benefits of tDCS and rTMS treatment for AN remain unclear. To date, tDCS and rTMS studies have varied in terms of treatment protocols (e.g., administered once or twice per day, up to 20 treatment sessions) and indicated limited efficacy and acceptability of both treatments. Further no study has directly compared the efficacy and acceptability of tDCS and rTMS. Here we propose to conduct the first double-blinded, randomised sham-controlled study to directly compare the therapeutic efficacy and acceptability of these two novel treatment modalities. This study will extend findings from previous studies in several ways, including: (1) using self-administered instead of in-clinic administered tDCS which has potential advantages for people living remotely or with restricted access to health care services; (2) using a newer form of patterned rTMS (intermittent theta burst stimulation: iTBS) which is much quicker to administer than standard rTMS; (3) administering an increased number of treatments and longer sham-controlled treatment period (8 weeks) compared to the only prior RCT of rTMS in AN (20 treatments) and previous studies (up to 4 weeks of acute treatment only); (4) the option of longer-term continuation at-home tDCS treatment to examine the potential for longer-term clinical benefits; (5) exploring participants’ experience of treatment though qualitative interview; and (6) extending the field of treatment strategies for AN expected outcomes including data on the relative efficacy, acceptability and cost effectiveness for both treatment modalities in the inpatient and at-home setting (i.e., for at-home tDCS). This will be important for informing a future larger definitive multicentre clinical trial. This pilot study’s main primary hypotheses are that both active treatment arms will produce clinical improvement in eating disorder psychopathology (measured with Eating Disorder Examination Questionnaire; EDE-Q; Fairburn [30]) at the end of 8-week randomised controlled period and that both active treatments will have high acceptability (measured with number of completed sessions for active tDCS and active rTMS in the acute 8-week RCT period).

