## Methods

### Design

This double-blind, randomised, sham-controlled trial will compare rTMS and tDCS acceptability and clinical outcomes in patients with AN. This study protocol was prepared in accordance with the SPIRIT and CONSORT guidelines. Participants will be randomised to one of four groups (2:1:2:1 ratio): active or sham tDCS, or active or sham rTMS. The brain stimulation protocols involve 84 sessions of tDCS (active or sham) or 56 sessions of rTMS (active or sham) over an 8 week treatment period. Participants in all groups will also receive treatment as usual (TAU) across the study duration. Following the end of 8 week randomised controlled period assessment, participants in all groups will have the option of receiving an additional open label 12 weeks of at-home, remotely supervised tDCS. A follow up assessment will be conducted at 20 weeks post treatment. A flowchart of the study is shown in Fig. 1.

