#### Primary outcomes

The efficacy and acceptability of rTMS and tDCS treatments will be this trial’s primary outcomes. The efficacy will be measured by a mean improvement of the Eating Disorder Examination Questionnaire (EDE-Q; Fairburn [30]) from baseline to end of treatment at 8 weeks. The EDE-Q is widely considered the gold standard tool for assessment of eating disorder (ED) psychopathology [1]. It is a self-report measure and includes four sub-scales related to the cognitive features of eating disorders: Restraint, Eating Concern, Shape Concern and Weight Concern. This measure for assessing change in the severity of eating disorder psychopathology was chosen due to its sensitivity in recognising behavioural and cognitive change in the recovery for AN [18]. Number of completed sessions for active tDCS and active rTMS in the acute 8-week RCT period will indicate acceptability of both treatments.

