#### Secondary outcomes

Analyses of secondary outcomes will be competed in the mITT population. The size of the treatment effect will be the difference in outcome data (BMI, questionnaires, neurocognitive outcomes) between the active and sham treatment arms for both tDCS and rTMS, respectively, at 4 weeks, 8 weeks, and 20 weeks post treatment. These effect sizes will control for pre-treatment scores. Descriptive statistics will be used to show remission rates for all treatment arms at post 8 weeks and 20 weeks post treatment. Generalised linear mixed models will be used to compare the treatment arms for mood and psychological symptom outcomes. Exploratory analyses will investigate associations between changes in mood and neurocognition with active tDCS and rTMS, and improvement in core eating disorder symptoms.

Generalised linear models will be used to compare cost and quality of life/utility values (from AQoL-4D) between treatments arms over the 8 week randomised treatment. Cost effectiveness analysis will compare the health outcomes and economic outcomes (costs of duration of inpatient stay and readmissions during the follow up period) associated with both treatment modalities.

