AN patients in previous studies were either in-patients receiving pharmacotherapy and psychotherapy [7] or out-patients with or without ED treatment [20, 21]. In this study, all participants will start as inpatients who will be receiving intensive concomitant treatment, i.e., comprehensive in-patient program with individual medication and/or psychotherapy and group cognitive behavioural therapy (CBT). This study will therefore explore, for the first time, the potential for additional therapeutic benefits of brain stimulation combined with existing eating disorders interventions.

AN has one of the highest treatment costs of any psychiatric disorder, largely due to the high cost of recurrent hospitalisation for nutritional rehabilitation [35]. Our study will explore the potential for these treatment modalities to reduce the length of hospital stays and emergency readmissions. Health economic data for both treatment modalities will additionally have utility from a service perspective, given the disparity in resource requirements between the two treatments (TMS, tDCS) in terms of costs for patients and access to treatment for people living in remote and rural areas (i.e., for at-home tDCS).

AN has been associated with impaired quality of life and lower preference-based health state utility values [2, 42, 49]. Utility values are used to calculate quality adjusted life years (QALYs) and used as an outcome measure by health technology assessment agencies such as the Pharmaceutical Benefits Advisory Committee in Australia and The National Institute for Health and Care Excellence in the UK. Our analysis will investigate the potential for these treatments to improve the quality of life and health state utility values for people with AN. This data will be useful for input into future trials and model based economic evaluations of these treatments.

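### The primary EDE-Q treatment effect is defined as uncontrolled pre-post change in the active arms, with no sham comparison, in a sham-controlled add-on trial

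*Protocol article*

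**What the plan says.** All references are to the Protocol article.

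- **Analysis, Primary outcomes.** The treatment effect on EDE-Q Global "will be the change in scores from pre-treatment to post 8 weeks treatment for both active treatment arms". The analysis is descriptive and graphical, in the mITT and PP populations. No sham term appears.
- **Outcome measures, Primary outcomes.** "The efficacy will be measured by a mean improvement of the Eating Disorder Examination Questionnaire" from baseline to week 8. No comparator is named.
- **Current study.** The primary efficacy hypothesis is that "both active treatment arms will produce clinical improvement in eating disorder psychopathology". Again no comparator is named.
- **Design.** The trial is double-blind, randomised and sham-controlled, with 2:1:2:1 allocation. "Participants in all groups will also receive treatment as usual (TAU) across the study duration".
- **Discussion.** "all participants will start as inpatients who will be receiving intensive concomitant treatment", and the trial is to explore "the potential for additional therapeutic benefits of brain stimulation combined with existing eating disorders interventions".
- **Analysis, Secondary outcomes.** For BMI, questionnaires and neurocognitive outcomes, the treatment effect is the difference "between the active and sham treatment arms for both tDCS and rTMS, respectively, at 4 weeks, 8 weeks, and 20 weeks post treatment", in the mITT population. "These effect sizes will control for pre-treatment scores".

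**The concern.** The design and the primary effect measure answer different questions. Randomising to sham within each modality, on top of usual care for everyone, identifies what stimulation adds. Pre-post change in the active arms shows how much those patients changed over eight weeks, for whatever reason. Patients enrolled during an inpatient admission and treated intensively can be expected to change, and those selected when unwell may regress towards their usual level.

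If the plan is followed as written, the main efficacy figure will carry the label of a treatment effect although the randomisation and the sham arms contribute nothing to it. The stated primary hypothesis could appear to be met with no stimulation effect at all. The trial's most important endpoint would also have a weaker effect measure than its secondary ones, such as BMI.

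**Working it through.** **Inputs.** From the article: 70 participants, allocation 2:1:2:1. The article gives no SD, correlation, dropout, alpha, power or expected change, so there is no figure of its own to reproduce. Everything marked as assumed below is not from the article.

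**1. What each measure estimates.** Let m be the expected EDE-Q change under sham (usual care, placebo response, regression to the mean, time) and D the effect added by stimulation. Then:

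- expected change in an active arm = m + D
- expected active-minus-sham difference = (m + D) − m = D

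The measure in the Analysis section, Primary outcomes, estimates m + D. The aim in the Discussion concerns D. The bias is m, and the article gives no information on its size.

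**2. Arm sizes.** 70 × 2/6 = 23.3 per active arm and 70 × 1/6 = 11.7 per sham arm, taken as 23 and 12 with no dropout assumed.

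**3. Illustration of how pre-post change can mislead.** Suppose D = 0 and m equals d standard deviations of change (assumed). For a two-sided 5% paired t-test with n = 23, the non-centrality is d × √23 on 22 degrees of freedom.

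| Assumed d | Non-centrality | Probability that one arm's 95% CI excludes 0 |
|---|---|---|
| 0.3 | 1.44 | 28% |
| 0.5 | 2.40 | 63% |
| 0.8 | 3.84 | 96% |

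The plan states no such test, so these are not error rates of the plan. They show only that a modest change unrelated to stimulation would readily look like improvement.

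**4. Precision of the controlled contrast, per modality.**

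- Unadjusted SE = SD × √(1/23 + 1/12) = 0.356 SD; 95% CI half-width = 1.96 × 0.356 = 0.70 SD.
- Adjusted for baseline with correlation r, multiply by √(1 − r²):
  - r = 0.5 (assumed): 0.698 × 0.866 = 0.60 SD
  - r = 0.6 (assumed): 0.698 × 0.800 = 0.56 SD
  - r = 0.7 (assumed): 0.698 × 0.714 = 0.50 SD

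**5. Comparison with pre-post precision.** With n = 23 the half-width is 1.96/√23 = 0.41 SD of change. At r = 0.5 the SD of change equals the SD of the score, since √(2(1 − 0.5)) = 1, so 0.41 compares directly with 0.60. The pre-post interval is narrower, but it is centred on m + D rather than D.

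**The case against.** **A sham-controlled EDE-Q contrast may already be planned.** The secondary analysis names questionnaires at 4, 8 and 20 weeks, and Table 1 schedules the EDE-Q at all three visits. A reader might infer from the primary text alone that EDE-Q is never compared with sham; the article does not support that. It is ambiguous, because the list under Outcome measures, Secondary outcomes, omits the EDE-Q. Even on the generous reading, the controlled contrast is secondary and mITT-only, and the uncontrolled change remains primary.

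**This is a descriptive pilot.** The article calls itself a pilot, acceptability is a co-primary outcome, and the primary efficacy text contains no test, alpha or success rule. It also matches the stated hypothesis, which speaks only of improvement in the active arms. All of this stands. It rules out reading the percentages above as a false-positive rate. It does not rescue the label: a descriptive effect size is still biased for what stimulation adds, and the mismatch with the sham-controlled design and the additional-benefit aim remains.

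**Further inferences that the article does not support.**

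- That participants with only a week-4 EDE-Q will be discarded, or that the lack of a mixed model for the EDE-Q is a fault. The article gives no rule for missing week-8 data, and such detail is commonly left to the full protocol or SAP.
- That the pre-post figure will set the size of a later trial. The article says only that results will inform future trials.
- That the report will credit the whole change to stimulation. This goes beyond the text, although the plan does call the change a treatment effect.

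**Conclusion.** The point holds as a fault in the definition of the primary effect. It is not missing detail: the article states an effect measure, and that measure is uncontrolled. It conflicts with the sham-controlled design, with the aim of finding benefit beyond intensive usual care, and with the article's own effect measure for secondary outcomes.

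The bias equals the change that would have occurred under sham, and the article does not allow it to be quantified. The 28%, 63% and 96% rest on assumed shifts and on a test that the plan does not contain, so they serve as illustration only. The half-width of about 0.6 SD rests on 23 v 12 with no dropout and an assumed baseline correlation of 0.5. Over correlations of 0.5 to 0.7 it runs from 0.60 to 0.50 SD. The controlled contrast is therefore estimable but imprecise, which is acceptable for a pilot that reports estimates with intervals.

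**What to change.** In the Analysis section, Primary outcomes, define the primary efficacy estimate as the baseline-adjusted active-minus-sham difference in EDE-Q Global at week 8, separately for tDCS and rTMS, each with a 95% confidence interval. Report within-arm change for all four arms as description, and do not call it a treatment effect. Bring the wording of the hypothesis in Current study and of the efficacy outcome in Outcome measures, Primary outcomes, into line. The existing mITT and PP populations can stay, and the method is the one already given for secondary outcomes.

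The cost is a dated change of wording, made before unblinding, and a little analysis work. It needs no new data, visits or participants. The estimate will probably be smaller than the pre-post change, and its interval will be wider (about 0.60 against 0.41 SD per modality at a correlation of 0.5). That width should be reported plainly as what a pilot of this size can show.

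### The primary acceptability outcome (completed sessions) is analysed in an mITT set that leaves out non-starters and those who leave before a first rating, so mean completion can be overstated

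*Protocol article*

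**What the plan says.** Under Outcome measures, Primary outcomes, the protocol article defines the outcome: "Number of completed sessions for active tDCS and active rTMS in the acute 8-week RCT period will indicate acceptability of both treatments". The matching hypothesis, at the end of Current study, is that "both active treatments will have high acceptability".

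Under Analysis, Primary outcomes, the analysis set is named: "The acceptability analysis will be completed in the mITT population". The method is descriptive: "Descriptive statistics will report the number of completed active tDCS and active rTMS treatments in the 8 week randomised controlled period".

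Under Analysis, Populations, the sets are listed: "The analysis will be completed for the Modified Intention to Treat (mITT) and the Per Protocol (PP) populations". The first is defined thus: "The mITT population will include all participants randomised and who had at least 1 randomised treatment and 1 post baseline rating". The per-protocol set is described as a subset of it, so no planned set contains everyone randomised.

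The section on adverse event monitoring says how sessions are recorded. The tDCS device logs the number of treatments given. Trained staff administer every rTMS session and record adherence.

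**The concern.** For most outcomes, an mITT rule of this kind is defended on the ground that a participant without treatment or follow-up has nothing to analyse. That defence is not available here. The first entry condition, at least one treatment, is the same as requiring the outcome to exceed zero. The second, a post-baseline rating, has nothing to do with whether sessions can be counted. The rule therefore selects participants partly on the outcome and cuts off its lower end.

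Non-starters can arise. Under Allocation, treatment is assigned before research treatment begins. tDCS participants must then be trained and credentialled before they treat themselves. Someone who declines or fails at that step has a known count of 0 and appears in no planned analysis.

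At stake is a primary result that is meant to inform a larger multicentre trial. If the reported mean omits those who never started or left very early, the later trial would plan on too optimistic a figure for completion.

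**Working it through.** **Inputs from the protocol article**
- Total sample 70, allocated 2:1:2:1 (Abstract, Methods).
- Planned sessions: "84 sessions of tDCS (active or sham) or 56 sessions of rTMS (active or sham") (Design).
- Schedules (Interventions): tDCS twice daily for 4 weeks, then daily for 4 weeks; rTMS twice per weekday for 4 weeks, then twice a day on 2 days a week for 4 weeks.
- Assessment times (Table 1): MADRS and DASS-21 from weeks 1–3; EDE-Q first repeated at week 4.

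**The plan's own figures**
- tDCS: 2×7×4 + 1×7×4 = 56 + 28 = 84.
- rTMS: 2×5×4 + 2×2×4 = 40 + 16 = 56.

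Both reproduce.

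**Size of an active arm:** 70 × 2/6 = 23.3, taken as n = 23.

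**Formula.** Let M be the mITT mean, x the number excluded from an arm, and e their mean number of sessions.

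All-randomised mean = [(n − x)·M + x·e] / n

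Overstatement = M − all-randomised mean = (x/n)·(M − e)

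The overstatement is positive whenever e is below M, and zero if nobody is excluded.

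**Illustration.** The document gives no exclusion rate, so x = 1, 3 and 5 and M = 90% of planned sessions are assumptions. With e = 0:

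| x of 23 | tDCS mean (mITT 75.6 of 84) | rTMS mean (mITT 50.4 of 56) | All-randomised, % of planned |
|---|---|---|---|
| 1 | 75.6×22/23 = 72.3 | 50.4×22/23 = 48.2 | 86.1 |
| 3 | 75.6×20/23 = 65.7 | 50.4×20/23 = 43.8 | 78.3 |
| 5 | 75.6×18/23 = 59.2 | 50.4×18/23 = 39.4 | 70.4 |

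If those excluded had completed 5 sessions each, the tDCS means become 72.5, 66.4 and 60.3 (86.3%, 79.0%, 71.7%), and the rTMS means 48.4, 44.5 and 40.5 (86.5%, 79.4%, 72.4%).

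With M = 80% and e = 0, the all-randomised figures are 76.5%, 69.6% and 62.6%. At M between 70% and 90%, each zero-session exclusion moves the mean by M/23, about 3 to 4 percentage points.

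**Which rating counts.** The definition does not say. If any scheduled rating counts, only non-starters and those who leave before an early MADRS or DASS-21 are lost. If the rating must be the EDE-Q, anyone who leaves before the week 4 assessment is lost. By the end of week 4 such a person could have completed up to 56 tDCS or 40 rTMS sessions. More participants could then be dropped, though each with a larger e, which makes the effect per person smaller than in the table.

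**The case against.** Several points on the other side have force.

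- **The set does not remove everyone who found treatment unacceptable.** A reader might infer that it does. The documents do not support this: a participant who stops after a first rating stays in with a low count. If an early MADRS or DASS-21 suffices, most dropout over the 8 weeks is retained. This stands and limits the point to non-starters and the earliest leavers.
- **Exclusions may be few.** All participants start as inpatients, rTMS begins during the stay, eligibility requires willingness to comply, and allocation follows consent. Five of 23 is 22% of an arm. These features make the upper illustrations less likely, but they do not make exclusions impossible.
- **No conclusion is predetermined.** It is tempting to say that the acceptability hypothesis is favoured by construction. But there is no numerical threshold for acceptability and no test, only a descriptive count in a self-described pilot. The figure can be inflated; no formal decision is flipped.
- **Bias between the modalities is only possible.** Start-up differs (self-administration after training against staff delivery), so exclusions could differ. Nothing in the document shows that they would, or in which direction.
- **A count of 0 is not always a verdict on the stimulation.** Some participants may not start for unrelated reasons, so an all-randomised mean mixes uptake with tolerance. This stands and is why reasons should be reported.

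An unseen analysis plan does not remove the point, since the article itself names the set for this outcome. None of these arguments gives a reason to omit known counts from the primary figure.

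**Conclusion.** The point holds in a limited form. The named set cannot contain a zero count and drops anyone who leaves before a first rating, although no rating is needed to know the outcome. Because the per-protocol set lies inside mITT, no other planned analysis makes this good. The direction is upward whenever those excluded completed fewer sessions than the rest, which is certain for non-starters.

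The size is unknown. For 1 to 5 zero-session exclusions per active arm of about 23, an mITT mean of 90% stands for about 86% to 70% of all randomised. This rests on the assumed number excluded, the assumed mITT mean and zero sessions among those excluded. The undefined rating adds uncertainty about how many participants could be lost.

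The point concerns acceptability only. A reader might extend it to the efficacy population or the role of the per-protocol analysis; nothing examined here supports changing either.

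**What to change.** Replace the sentence that names the acceptability population with one to this effect: completed sessions will be reported for all participants randomised to each active arm, as allocated, with non-starters counted as 0 and withdrawals at the number of sessions completed. Add that the number excluded from mITT and the reasons will be given per arm, so that non-starts unrelated to the stimulation can be seen, and that the mITT figure will be shown as supportive. State in the mITT definition which post-baseline rating is meant.

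The cost is small: the text changes are short and the session data are already being collected. The downside is a somewhat less favourable acceptability figure, which will also reflect non-starts that have nothing to do with the stimulation.

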### Interventions

#### Repetitive transcranial magnetic stimulation (rTMS)

rTMS will be administered using a MagPro TMS device. rTMS involves the application of transient magnetic pulses which induce small currents in the underlying cortex via the principal of electromagnetic induction. Both sham and active rTMS will be commenced while participants are inpatients and will continue over the 8 weeks of acute treatment. rTMS will be twice per weekday (separated by ≥ 2 h) [53] over the first 4 weeks (Monday-Friday) and then twice daily per day (separated by ≥ 2 h), given on 2 days each week for the following 4 weeks. Treatment every weekday for 4 weeks is consistent with a typical therapeutic course for intermittent theta-burst stimulation (iTBS) [9]. A taper period over the following 4 weeks is consistent with clinical recommendations for rTMS [59] and has been designed to coincide with participants attending the hospital for day patient programs, 2 days per week, or continuing in outpatient care following discharge from the inpatient program. Active rTMS will be administered using a patterned frequency stimulus called intermittent theta-burst stimulation (iTBS) [40]. This form of rTMS was chosen because a recent large multicentre trial showed 3 min of iTBS attained the same therapeutic effect as 30 min of standard rTMS, leading to FDA approval for depression [9]. Each rTMS treatment session will comprise an extended iTBS session, i.e., 6.6 min, delivered at 100% resting motor threshold (RMT). Extended iTBS has previously been found safe and effective in patients with depression [15]. It will be targeted to the left DLPFC (based on F3 using the 10-20 International EEG system), consistent with the prior RCT of rTMS for AN [20, 21]. For sham rTMS, a sham coil will be placed on the head with no active stimulation administered.

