#### Transcranial direct current stimulation (tDCS)

tDCS will be self-administered using the 1 × 1 tDCS mini-CT Stimulator (Soterix, USA: ARTG: 284637) with two saline-soaked sponge electrodes held in place on the scalp using the Soterix Ole-2 headband [72]. The device is intended to treat different neurological and psychiatric disorders. tDCS involves the passing of weak electrical current through the brain via electrodes placed upon the scalp. The current modulates the resting membrane potential of stimulated neurons which causes changes in neuronal excitability. The anode will be placed over the left F3 (10-20 System) and the cathode over F4 (electrode sizes 5 × 5 cm, 25 cm^2^) using the BEAM F3 method [61]. This montage was chosen to target the left DLPFC, consistent with prior studies of tDCS in AN [7, 45, 71]. Sham and active tDCS will be given 84 sessions over 8 weeks of TAU: twice daily (separated by ≥ 2 h) over the first 4 weeks, and daily over the second 4 weeks of the 8 week treatment period. Twice daily tDCS was found safe and effective in previous pilot trial in AN [71]. Active tDCS will be given continuously for 30 min at 2 mA. Sham tDCS will involve an initial ramping up to 1.0 mA and then a ramp down to 0 mA, with a similar ramp up and down at the end of the treatment. Participants receiving active or sham tDCS will self-administer treatment after receiving training, practice and credentialling consistent with our home-based tDCS protocol [3]. The research team will routinely monitor participant’s adherence to the intervention protocol and side effects from each treatment recorded on the Soterix Medical ElectraRx platform. The Soterix Medical ElectraRx solution is a software portal connecting stimulation administrators/clinicians and individuals with the data collected from Soterix Medical neuromodulation technologies including tDCS. At all times, the research team will have real-time access to the information collected by the individual’s device. They will also have access to the individual’s historical data, side effects, stimulation compliance, and warning signs.

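### Acceptability is a raw count of completed sessions, but tDCS schedules 84 and rTMS 56, so the unscaled counts cannot be compared between modalities

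*Protocol article*

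**What the plan says.** The protocol article words the acceptability outcome in the same way in three places. In Current study, the hypothesis of high acceptability for both active treatments is "measured with number of completed sessions for active tDCS and active rTMS in the acute 8-week RCT period". Under Outcome measures, Primary outcomes: "Number of completed sessions for active tDCS and active rTMS in the acute 8-week RCT period will indicate acceptability of both treatments". Under Analysis, Primary outcomes: "Descriptive statistics will report the number of completed active tDCS and active rTMS treatments in the 8 week randomised controlled period", and "The acceptability analysis will be completed in the mITT population".

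The two modalities do not have the same number of sessions. Design states: "The brain stimulation protocols involve 84 sessions of tDCS (active or sham) or 56 sessions of rTMS (active or sham) over an 8 week treatment". The Discussion repeats both totals.

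The Abstract, Design and Discussion each say that the trial will compare acceptability between tDCS and rTMS. None of these places scales the count to the number scheduled. The only proportional measure of adherence is in Populations, where the per-protocol set requires at least 80% of the randomised treatments. That rule defines an analysis set and not the acceptability outcome, which is analysed in the modified intention-to-treat population.

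**The concern.** A count of completed sessions depends on how willing and able participants are to complete treatment, and on how many sessions they were offered. When the number offered differs by half between the groups being compared, the count reflects the schedule as well as acceptability. Two groups with identical adherence get different scores, and the group with poorer adherence can get the higher one.

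The hypothesis within each arm is affected too. It predicts high acceptability for both treatments, but a given number of sessions does not mean the same thing in the two arms.

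The article says that the results are meant to inform a larger definitive trial. A difference that comes only from the denominators could then be taken as evidence for one modality.

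**Working it through.** **Inputs.** The scheduled totals of 84 and 56 come from Design. The tDCS schedule is in the tDCS section: "twice daily (separated by ≥ 2 h) over the first 4 weeks, and daily over the second 4 weeks of the 8 week treatment period". The rTMS schedule is in the rTMS section: two sessions per weekday for four weeks, then two sessions on each of two days a week for four weeks. The 80% level comes from Populations. The article gives no expected adherence, so every adherence level below is an assumption for illustration.

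**Reproducing the plan's totals.**
- tDCS: 2 × 7 × 4 + 1 × 7 × 4 = 56 + 28 = 84.
- rTMS: 2 × 5 × 4 + 2 × 2 × 4 = 40 + 16 = 56.

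Both agree with Design.

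**Equal adherence.** Expected count = adherence × scheduled sessions. The ratio of counts is 84/56 = 1.5 at any common adherence.

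| Adherence in both arms | tDCS count | rTMS count | Gap |
|---|---|---|---|
| 100% | 84 | 56 | 28 |
| 90% | 75.6 | 50.4 | 25.2 |
| 80% | 67.2 | 44.8 | 22.4 |
| 50% | 42 | 28 | 14 |

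As a percentage of scheduled sessions, the gap is zero in every row.

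**Unequal adherence.** tDCS has the higher count when 84 × (tDCS adherence) > 56 × (rTMS adherence), that is, when tDCS adherence exceeds 56/84 = two thirds of rTMS adherence. The break-even tDCS adherence is 66.7% when rTMS is at 100%, 60% when rTMS is at 90%, and 53.3% when rTMS is at 80%.
- tDCS 70%, rTMS 95%: counts 58.8 and 53.2. The count favours tDCS and the percentage favours rTMS.
- tDCS 60%, rTMS 95%: counts 50.4 and 53.2. This is below the break-even of 63.3% (95% × 2/3), and both measures favour rTMS.

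**Single participants, against the plan's own 80% level.** No rTMS participant can exceed 56 sessions. The 80% level for tDCS is 0.8 × 84 = 67.2 sessions. A tDCS participant with 57 to 67 sessions (57/84 = 67.9% to 67/84 = 79.8%) therefore misses the per-protocol adherence criterion, yet has a higher acceptability count than an rTMS participant who attended every session.

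**Within-arm meaning.** Fifty completed sessions are 50/56 = 89% of the rTMS course but 50/84 = 60% of the tDCS course.

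**The case against.** The strongest reply is that the article specifies no analysis that ranks, subtracts or tests counts between modalities. The outcome is summarised descriptively in each active arm, and the stated hypothesis is about each treatment separately. Each arm has one fixed, published denominator, so an arm mean becomes a percentage by one division. The 80% rule shows that the trial team already thinks of adherence in proportional terms. The article also condenses a full protocol that is not shown, and its wording does not forbid a percentage beside the count.

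Much of this stands, and it limits the weight of the point. It does not remove it. The measure is stated three times, always as a number, so this is a choice that the document fixes and not a detail left out. The comparison is a declared aim even though no test is attached. The proportion of participants reaching 80% cannot be recovered from a mean count. Settling the scale of a primary outcome after the results are known is best avoided.

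A percentage is not a perfectly neutral measure either. Self-administered sessions every day and staff-delivered sessions on selected days differ in burden even after rescaling. That is a reason for care in interpretation, and the planned interviews on treatment experience will help. It does not favour the raw count.

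A reader might infer three stronger points, none of which the article supports:
- **That tDCS will come out ahead however poor its adherence.** It does so only above two thirds of rTMS adherence.
- **That the count cannot answer the question at all.** With the published totals, the arm-level percentage can be recovered.
- **That reporting the active arms alone is an error.** The hypothesis concerns the active treatments, and adherence is recorded in all arms, so a sham comparison remains possible. Whether to show it is a matter of preference.

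**Conclusion.** The point holds as one that should be corrected. As defined, the acceptability outcome is not comparable between tDCS and rTMS. Equal adherence always gives tDCS a count 50% higher (22.4 sessions at an assumed 80%), and the ordering is reversed whenever tDCS adherence is lower than that of rTMS but still above two thirds of it.

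The factor of 1.5 and the two-thirds limit follow from the scheduled totals alone. The session gaps also depend on the assumed adherence levels. The point does not rise to a critical flaw: the analysis is descriptive, no decision rule in the article depends on the count, the arm means can be rescaled, and no data are lost.

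**What to change.** In Current study and in both Primary outcomes sections, define acceptability as each participant's percentage of scheduled sessions completed in the 8-week randomised period: n/84 for tDCS and n/56 for rTMS. Keep the raw count beside it. For each active arm, report:
- the mean percentage with its 95% confidence interval;
- the proportion of participants reaching the 80% level already used in Populations.

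Report also the tDCS-minus-rTMS difference in mean percentage between the active arms. Showing the sham arms on the same scale is optional.

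The cost is a few words in three places. The session records described in the tDCS and Adverse event monitoring sections already supply the data, and neither the treatment schedule nor the sample size changes. The change should be recorded before the database is locked.
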